## 5. Conclusions

People with CP have particular difficulties in recognizing both their mood and fatigue. This means that in rehabilitation routines or in the performance of physical activity, it is sometimes difficult to properly program the exercise so that they find it motivating and get the most out of the time devoted to such activity.

There are questionnaires that allow the measurement of both the emotional state [35] and the fatigue state [36], but a user with CP does not always have the necessary cognitive and communication skills to rely on these questionnaires.

It is necessary to resort to more objective methods, and the measurement of biosignals is a good alternative. But in order to rely on biosignals, it is necessary to study whether the changes generated in the biosignals are significant. To determine this, it is necessary to put the subjects in contexts where we can predict and control for what their mood is going to be. These contexts are often activities that are part of their daily routines and for which we have experience of their previous responses. The caregivers and the family environment should support the choice of the routines where the biosignals will be recorded. Whenever possible, these measures can be reinforced with tests to measure emotions and physical state by the subjects themselves or their caregivers, in cases where the subject does not have physical or cognitive abilities to complete them. On the other hand, signal processing should be performed to extract parameters that should then be studied statistically to assess their robustness in determining a state. It is also important to assess how physical movement affects a person’s biosignal data. Appropriate techniques should be studied to eliminate the noise produced by this factor so that it does not affect the extraction of accurate information about the condition. To implement the approach outlined in this paper, two sessions, denoted as sessions 1 and 2, have been devised. Session 1 aims to induce a state of pleasant emotion, while session 2 aims to induce discomfort. These sessions enable us to establish correlations between the parameters derived from the inertial sensors or biosignals being recorded and various emotional states. This process helps identify the most reliable parameters to gauge the users’ states across different contexts objectively. Section 3.3.2 enumerates and elucidates all parameters relevant to the various types of recorded signals. Following the proposed data analysis in Section 4.2, we will select the parameters that most effectively discriminate the physical and emotional states of the subjects.

In addition, we want to evaluate how music can be a motivational factor that improves the quality and time dedicated to physical exercise. Therefore, in the proposed experimental protocol, we will introduce an analytical study of type AB in the second part. In Section 2, the review of the state of the art, we presented previous studies with the common finding that musical parameters can induce emotions and the measurement of the EEG signal can be a primary method for showing their change. The proposed protocol will take these factors into account when choosing music and will also introduce the measurement of other types of additional physiological signals.

To operationalize this, sessions 3 and 4 of the experimental protocol have been devised. Music is introduced as a motivational element, and its impact is assessed using the parameters established in sessions 1 and 2. The goal is to enable subjects to invest more time and effort in their rehabilitation sessions, as the achievement of an optimal emotional and physical state during these sessions can be reliably and objectively monitored.

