#### 3.3.3. Contexts and Measurement Frequencies

Four sessions will be held, each divided into two parts:

Selection of dependent variables: The objective of the initial two sessions is to establish a baseline for physiological variables during activities that elicit both positive and negative emotions, to use this baseline as a reference in Part 2. The goal is to minimize the reliance on the EVEA tests, as participants may not always be able to articulate their emotions. The EVEA test serves as a supporting tool for a potential automatic classifier.

Session 1: Measurement of parameters when the subject is conducting a pleasurable daily-life activity in the center.Session 2: Measurement of parameters when the subject is conducting an uncomfortable daily-life activity in the center.These sessions will be determined by conversation with the caregivers since they are specific to each subject.

Half of the participants will start with session 2 and then do session 1, while the rest will follow the reverse order.

Music’s influence on the dependent variables: The aim of the next two sessions is to determine the music’s influence on the dependent variables while conducting rehabilitation exercises.

Session 3: Measurement of subject parameters during the performance of rehabilitation activities in the center.Session 4: Measurement of subject parameters during rehabilitation activities in the center. This session will be accompanied by music according to the preferences of the subject.

Each participant will select the music to be played in each session according to their musical preference or, failing that, the music will be selected by their caregiver. The rehabilitation activity should be a gentle exercise for the participant, such as pedaling, extending the limbs or any other activity that can be quantified using inertial units. Furthermore, these activities should be determined by the medical/physiotherapist staff according to the capabilities of each volunteer.

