Even though every session has a unique theme, the format of the sessions will remain consistent. The sensors will initially be placed on the participant and a data acquisition test will be performed to ensure that all data are being captured correctly. Data recording will initiate while the user is responding to the EVEA test; this phase will be used as a baseline for the session—note that a minimum of two minutes is required. The following phase will be the main activity, with a 15 min time limit, ending with a final EVEA test with identical specifications to the initial one, which will be used as the final baseline. Both baselines allow for the detection of the measurement differentials in each session, alongside the analysis of the participant’s progression during the activity. Each participant is expected to finish the protocol within two weeks, where the first and second sessions will be scheduled for the first week, and the third and fourth sessions will be set for the second one. Figure 4 shows a diagram of the described protocol.

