### 4.2. Data Analysis

In general, numerical variables will be expressed as mean (M) and standard deviation (SD), including range, minimum and maximum.

For the first part of the study, we will compare the dependent variables obtained between sessions 1 and 2 for each subject using the permutation test of the difference in means between different data windows. Those dependent physiological variables that mark significant differences for most of the subjects will be chosen. Changes in EVEA test responses between sessions 1 and 2 will serve as reinforcement for detecting the level of emotional change.

We will also correlate the results of the EVEA test with the base state questionnaires to determine the existence of some type of dependency between the base level of EVEA and its variation with respect to the base state. This dependence will be explored with the Spearman or Pearson correlation test.

For the second part, first, we will analyze the variation in EVEA for sessions 3 and 4 to determine if there is a significant dependence on the independent variable (music) between stages A and B for all the participants. We will use the Kruskal–Wallis test, which does not require any type of assumption regarding the normality and homoscedasticity of the samples. These variations will also be correlated with the quality of life scale (ICF, GMFCS, MACS, CFCS, or KIDSCREEN), as was carried out with the data from the first part.

For the physiological variables and the average kinetic energy, we will determine if their variations are significant between A and B by means of a Kruskal–Wallis test applied to the group of subjects, but also at the individual level by means of a permutation test.

The significance of the tests will be set at three levels, indicated with * (*p* < 0.05), ** (*p* < 0.01) and *** (*p* < 0.001).

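### Part 1 selects emotion parameters from one session per state, so it shows discrimination between two single sessions, not the reliability across contexts claimed in the Conclusions

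*Protocol article*

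**What the plan says.** Section 3.3.3 gives each subject one recording of each state: "Session 1: Measurement of parameters when the subject is conducting a pleasurable daily-life activity in the center" and "Session 2: Measurement of parameters when the subject is conducting an uncomfortable daily-life activity in the center". Half of the participants take these two sessions in reverse order. All four sessions share a format. Recording starts during a first EVEA of at least two minutes, and "this phase will be used as a baseline for the session"; an activity of up to 15 minutes and a final EVEA follow. The two baselines are meant for differences and progression within a session.

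Section 4.2 compares sessions 1 and 2 in each subject "using the permutation test of the difference in means between different data windows", and then: "Those dependent physiological variables that mark significant differences for most of the subjects will be chosen". The test is named again for the individual comparison of sessions 3 and 4 (silence versus music).

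Section 5 describes the result as follows: the process "helps identify the most reliable parameters to gauge the" users' states objectively in different contexts. The selected parameters are then used to assess music, with the aim that the subject's state "can be reliably and objectively monitored".

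**The concern.** A parameter is reliable if it returns a similar value when the same person is measured again in the same state, and a different value in another state. Part 1 never measures the same state twice, and section 4.2 names no within-subject SD, intraclass correlation or other yardstick for ordinary change between sessions.

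All windows of one session share whatever was particular to that session, such as sensor placement, time of day or tiredness. The permutation test exchanges single windows between the two sessions, so it counts a common shift of this kind as a difference between states. The stated rule also does not ask that the difference go in the same direction across subjects. A variable that wanders between sessions can therefore be selected as an emotion marker. In Part 2, where silence and music are again recorded once each, another shift of the same kind could be read as an effect of music.

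**Working it through.** **The plan's own figure.** Section 4.1 has N = 200, p = q = 0.5, 95% confidence and a 15% margin.

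- n0 = 1.96² × 0.25 / 0.15² = 42.68
- n = 42.68 / (1 + 41.68/200) = 35.32, rounded up to 36

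The 36 reproduces. It serves here only as the number of subjects, so that most means at least 19 of 36. Section 3.2 plans 40 subjects, for which most means at least 21.

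**How a session shift enters the test.** Assumptions: no emotion effect, independent windows, m windows per session, and a share ρ of within-subject variance lying between sessions. The article gives neither m nor ρ.

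- True variance of the difference in session means: 2[ρ + (1 − ρ)/m]
- Variance the window test works with: about 2(1 − ρ)/m
- Ratio: 1 + mρ/(1 − ρ)

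For m = 15 and ρ = 0.2 the ratio is 1 + 15 × 0.25 = 4.75. The large-sample false-positive rate is then 2[1 − Φ(1.96/√4.75)] ≈ 0.37.

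**Simulation.** 20,000 runs per setting, with a two-sample t-test standing in for the permutation test at 0.05. The chance of selection is the binomial probability of at least 19 of 36 subjects.

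| Windows per session | ρ | False-positive rate per subject | Chance of selection |
|---|---|---|---|
| 5 | 0.1 | 0.10 | <0.001 |
| 5 | 0.3 | 0.23 | <0.001 |
| 5 | 0.5 | 0.38 | 0.046 |
| 15 | 0 | 0.05 | <0.001 |
| 15 | 0.1 | 0.22 | <0.001 |
| 15 | 0.2 | 0.36 | 0.03 |
| 15 | 0.3 | 0.46 | 0.24 |
| 15 | 0.5 | 0.61 | 0.89 |
| 30 | 0.1 | 0.35 | 0.02 |
| 30 | 0.2 | 0.49 | 0.41 |
| 30 | 0.3 | 0.60 | 0.84 |
| 30 | 0.5 | 0.72 | >0.99 |

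With 40 subjects the results are close: 0.04 for 5 windows, 0.90 for 15 and >0.99 for 30, all at ρ = 0.5. A true permutation test with 15 windows gave per-subject rates of 0.06, 0.34 and 0.61 at ρ = 0, 0.2 and 0.5, in line with the t-test.

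**What the recorded data can supply.** Each subject has four initial phases. For a one-way intraclass correlation r with k = 4, F = (1 + 3r)/(1 − r), and the 95% limits come from F quantiles with n − 1 and 3n degrees of freedom. An assumed r = 0.70 gives F = 3.1/0.3 = 10.33 and these limits:

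- n = 36 or n = 40: 0.57 to 0.81
- one age group, n = 18: 0.50 to 0.86

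At n = 36, r = 0.50 gives 0.33 to 0.67 and r = 0.90 gives 0.84 to 0.94. Noise in the baseline level can therefore be estimated usefully without new recordings.

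**The case against.** The word reliable stands in a hedged sentence of the Conclusions, and the same section goes on to say that the parameters which discriminate best will be selected, which is what section 4.2 does. The remark on reliable monitoring belongs to a statement of the project's goal. This softens the wording but leaves two different properties treated as one.

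The plan has protections. Significance in most subjects is replication across people, and it works well when session noise is small or windows are few, as the table shows. The reversed order balances systematic order effects over the group. The initial and final baselines could remove much of a level shift, although section 4.2 does not say that the tests use change from baseline. None of these, as the rule is written, removes a random session shift within a subject.

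An additional repeatability statistic could be left to an analysis plan. The selection rule itself, however, is fixed in the article, and the reliability statement is attached to it.

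Two stronger readings are tempting and not supported:

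- A reader might infer that the four initial phases already provide the missing reliability. They repeat one common condition, recorded during the EVEA before activities of different kinds. They show noise in the baseline level, not whether the response to a pleasant or unpleasant state repeats.
- A reader might want a fixed cut-off, keeping a variable only if its change exceeds the repeatability limit of 1.96 × √2 = 2.77 between-session SDs. That limit applies to one person's pair of measurements. Take a difference of 1.0 and an SD of 0.75 on an arbitrary scale. The limit is 2.08, so the variable would be dropped. If the effect is the same in all 36 subjects, the SD of the difference is 0.75 × √2 = 1.06, its standard error 1.06/6 = 0.177, and paired t about 5.7, a clear group effect. A cut-off could also reject a variable because it follows mood, which may differ between initial phases.

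**Conclusion.** The point holds in this form: the selection rule shows discrimination between two single sessions, and the reliability claims in section 5 go beyond it. Under the assumptions above, the chance of selecting a parameter with no emotion effect runs from below 0.05 (5 windows, share up to 0.5) to about 0.9 or more (15 to 30 windows, share 0.5). Where this study lies in that range cannot be told from the article. It does not follow that the selected parameters will be wrong, or that a music effect in Part 2 would be an artefact. The plan simply gives no means of judging either. Because the repair is cheap and the selected variables carry Part 2, the change should be made.

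**What to change.** In section 4.2:

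- Estimate each variable's within-subject between-session SD and intraclass correlation from the initial phases of sessions 1 to 4.
- Report the session 1–2 change against that SD, preferably taking each session's value as the change from its own initial phase.
- Take this comparison into account when choosing variables for Part 2, without a fixed 2.77 × SD cut-off.
- State that it measures baseline noise only, not repeatability of the response to the pleasant or unpleasant state.

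In section 5, replace the claims of most reliable parameters across contexts and of reliable monitoring with *most discriminating between the two sessions*. The stronger wording would need each state to be recorded more than once.

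Cost: a little more analysis on data already recorded. The noise estimate is approximate, since the initial phase is short, is recorded during the EVEA and may itself vary with mood.

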## Figures and Tables

**Figure 1 jpm-14-00521-f001:**
[figure not shown]
System used in signal recording.

**Figure 2 jpm-14-00521-f002:**
[figure not shown]
EEG channels selected in the 10/20 system. The position of the ground electrode is marked in red, selected channels in blue, and the reference placed on the earlobe is in green.

**Figure 3 jpm-14-00521-f003:**
[figure not shown]
LabRecorder software for synchronized data logging.

**Figure 4 jpm-14-00521-f004:**
[figure not shown]
Scheme of the protocol. (**a**) Activities and timing of the global protocol. (**b**) Activities to perform during a session.

**Table 1 jpm-14-00521-t001:** Questionnaire for users [9]. The choices were yes (Y), no (N), and no answer/do not know (NA).

	Question	Choices
Q1	I liked the activity.	Y, N, NA
Q2	I felt good after the activity.	Y, N, NA
Q3	I felt good before the activity.	Y, N, NA
Q4	I have finished very excited.	Y, N, NA
Q5	I have finished very bored.	Y, N, NA
Q6	I have finished very overwhelmed.	Y, N, NA
Q7	I have finished the activity with pain.	Y, N, NA

**Table 2 jpm-14-00521-t002:** Questionnaire for caregivers [9]. The choices were very low (VL), low (L), normal (N), well (W) and very well (VW).

	Question	Choices
Q1	The care receiver has done the suggested activity as it is described?	VL, L, N, W, VW
Q2	Suggested activity was appropriate for the patient.	VL, L, N, W, VW
Q3	Suggested activity was appropriate at the time it was recommended.	VL, L, N, W, VW

## Data Availability

The data obtained in this research will be hosted in the repository of the University of Seville (https://idus.us.es/).

## Abbreviations

The following abbreviations are used in this manuscript:

AAI	Augmentative Affective Interface
AI	Artificial Intelligence
AIR4DP	Artificial Intelligence and Robotic Assistive Technology devices for Disabled People
AMIGOS	A dataset for Multimodal research of affect, personality traits and mood on Individuals
	and GrOupS
ASPACE	Association of People with Cerebral Palsy of Seville
CFCS	Communication Function Classification System
CP	Cerebral Palsy
ECG	Electrocardiogram
EDA	Electrodermal Activity
EEG	Electroencephalography
EVEA	Scale for Mood Assessment
FACS	Facial Action Coding System
FD	Fractal Dimension
FMRI	Functional Magnetic Resonance Imaging
GMFCS	Gross Motor Function Classification System
GSR	Galvanic Skin Response
HF	High Frequency
HR	Heart Rate
HRV	Heart Rate Variability
ICF	International Classification of Functioning, Disability and Health
LF	Low Frequency
M	Mean
MACS	Manual Ability Classification System
pNN50	Percentage of successive RR intervals that differ by more than 50 ms
PNS	Parasympathetic Nervous System
PSD	Power Spectral Density
RMSSD	Root Mean Square of Successive Differences between normal heartbeats
SCL	Skin Conductance Level
SCR	Skin Conductance Response
SD	Standard Deviation
SDNN	Standard Deviation of NN intervals
SE	Spectral Entropy
SNS	Sympathetic Nervous System
TAIS	Technology for Assistance Integration and Health
VR	Virtual Reality
